### Data management and quality assurance

The dental care organization staff members who have been trained by UW investigators will collect data. Data will be entered in a secure and US Health Information Portability and Accountability Act of 1996-compliant database with range checks for data values. Although we do not expect any adverse events to occur, staff members will be trained to collect, report and manage solicited and spontaneously reported adverse events and other unintended effects of trial interventions or trial conduct. UW investigators do not have access to personal health information and receive only de-identified datasets for analysis.

### Ethics and dissemination

The results from the trial will be published regardless of the outcome. Reporting of this trial will adhere to the relevant and most up-to-date CONSORT [11] and SQUIRE [12] statements and relevant extensions [13, 14]. The investigators ensure that the trial is conducted in compliance with this protocol and federal regulations. The protocol was submitted to and considered by the University of Washington Institutional Review Board, but, consistent with US Federal regulations, participants of this quality improvement project do not meet the criteria to be considered research subjects and ethical approval was deemed unnecessary.

## Discussion

In most states, children enrolled in the Medicaid program have low utilization of dental care and a high prevalence of untreated decayed teeth. Barriers to care and per patient treatment costs can be substantially reduced by a population-based approach to dental care and the provision of basic services outside of traditional clinics. Total expenses increase because more children and mothers receive care. This alternative model does not depend on caregivers taking children to dental offices during work time and can achieve substantial savings in capital costs associated with facilities and equipment and personnel. Children at high risk can be identified and intensive evidence-based effective preventive and curative services provided.

To our knowledge, this intervention will be the first large scale, “real world” test of an alternative delivery and payment model that has the potential to reduce dental care and oral health disparities nationally. This delivery model is replicable in the 47 states where dental hygienists are legally able to provide services to low-income children in community settings under indirect dentist supervision (for example, dentist is not physically present but is on call).

The major challenges for PREDICT are obtaining the permission of community organizations and schools to implement the new dental care system, gaining the cooperation of community leaders, educators, principals and teachers, and getting parents to sign-up for the program. Another challenge is providing the screening, risk assessment and risk-based services to children at community settings cost-effectively. Finally, children with dental diseases or other oral health needs that require treatment in dental offices need to receive it in a timely fashion through well-organized pathways.

Both the evaluation and effective management of this intervention depend on the availability of operational data. First, staff members have to complete annual environmental scans of test and control counties. These scans address differences among counties in availability of dentists, community prevention programs, population income and ethnicity, etc. Second, data are needed on community settings and schools for planning the intervention and evaluation. Third, data are needed on the characteristics and oral health of the children who do/do not consent for the program. Finally, the costs and services provided in test and control dental delivery systems need to be assessed. Determining the categories of cost that are incremental to evaluation versus care delivery (for example, analysis costs and any space, time, and supply costs unique to the evaluation) will also be important. This requires a clear understanding and measurement of all costs, so costs specific to the evaluation can be identified. Realistically, the final cost assignment is best done retrospectively. This is because some evaluation costs may cover business or clinical processes that turn out to be critical for the effective management of the program. As such, they should be considered care delivery costs.

The key to this intervention is effective management and HIT support. Managers and staff members need monthly management reports so they can adjust to problems that arise. ADS has substantial public relations and financial risk, so it is incentivized to make an all-out implementation effort. This “real’ world” operational environment increases the chances for success and the generalizability of the results. Indeed, if the intervention is cost-effective, ADS plans to make it the primary delivery model for Medicaid children and mothers.

The role of financial incentives in the proposed intervention has special importance. Most incentive plans try to influence the behaviors of the dominant providers, in this case, shareholder and employed dentists. However, a careful assessment of the actual intervention indicates that the EPPDHs and administrative staff are the main drivers of program success. This is because only 25 to 30 % of assigned patients will need to be seen by dentists for curative care in the first few years of the program. Moreover, this proportion will decline as the backlog of disease is treated, and new disease is prevented. Developing sensible incentive plans for the nonprofessional staff is not easy, and this will be one of the first studies to address this issue on a large scale in dentistry or medicine. The incentive plan has to take into account the culture of the organization, the interests of the staff in the intervention program, and other factors. For this reason, incentives are mainly positive rather than negative. That is, high performance is rewarded financially, but average or poor performance does not result in substantial reductions to base pay. In the case of below-average performance, emphasis instead is on performance feedback and development of a specific improvement plan.

In summary, we have presented the trial protocol for the PREDICT quality improvement project and discussed the challenges in implementing and evaluating this new dental care delivery and payment systems in a large dental care organization serving Oregon rural counties.

### Trial status

The quality improvement project started in October 2014, and counties have been identified and randomly allocated. Delivery system and payment system changes will be deployed in August 2015 and January 2015, respectively. Data collection for the parent/caregiver/child and staff surveys will be conducted in July and August 2015 and in September and October 2017. The study is not yet recruiting participants.

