#### Timing of recruitment, intervention delivery and follow-up

Identification of the clusters (counties) and randomization to test and control interventions was concluded in October 2014. The first phase of the project has been initiated, including the rewriting of job descriptions, identification of appropriate staff members, refinement of outcome metrics, and initial development of IT systems to support the service delivery and incentive payment changes. Formal training of staff will begin in spring 2015; the implementation of the new delivery system will begin in summer 2015; full project implementation will begin when schools open in September 2015 and will last for 24 months. Baseline assessments will be conducted during summer and fall 2015 and final assessments during summer and fall 2017.

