#### PREDICT - the program

In the seven test counties, Expanded Practice Permit Dental Hygienists (EPPDH) will obtain the consent for treatment at community settings and provide selected primary dental services in non-traditional settings and refer patients to primary care dentists and specialists for complex treatments. Community liaisons and case managers, serving as patient navigators, will help the EPPDH obtain the consents and assure that needed treatments are completed at community and dental office settings. This new delivery system is supported by a financial incentive system for high performance (pay-for-performance, capitation payment and global budget) and by an efficient information system for performance monitoring. The service delivery and payment changes focus on the following: 1) identifying Medicaid-eligible children, pregnant women and new mothers and gaining caregiver consent for services in community settings (for example, schools, Head Start, and WIC Centers); 2) providing risk-based preventive and caries stabilization services efficiently at these settings; 3) providing seamless, effective curative care in dental clinics; and 4) incentivizing local delivery teams to meet performance benchmarks.

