#### Data collection

Data on *impact outcomes* will be obtained through a clinical examination of children and a telephone survey of parents/caregivers and children at baseline and after 24 months. A random sample of Medicaid-enrolled ADS-assigned children will be obtained and stratified by county, at baseline and 24 months post-implementation. The sample will include children whose caregivers either consented or did not consent for care. It will also include children who sought care directly from a dental office. For the survey, staff members will be given a list of enrollees to telephone and move down the list in order until the required sample size is reached. Each individual will be called a minimum of five times. For the clinical examination, staff members will be given a list of enrollees, and they will exam the children in the community settings.

Data on *process and cost outcomes* will be obtained through ADS’s health information systems: Medicaid enrollment database, ADS database (ADIN), electronic dental records and payroll ledger. All Medicaid-enrolled ADS-assigned children population will be included in the process and cost evaluation. Enrollment information including patient identifiers, birth date, gender, race/ ethnicity, coverage dates and assigned primary care provider will be obtained from ADS’s enrollment database and linked to State Medicaid claims. Medicaid claims will be accessed to collect emergency department, medical care and prescription services and costs. Data on *structure outcomes* will be obtained through staff online surveys at baseline and after 24 months and continuously through ADS’s health information systems and internal records. Fidelity information will be obtained through staff surveys and internal records.

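### Baseline caries examinations scheduled into fall 2015 follow the start of the delivery change, and the stated payment date precedes all baseline work, so the pre-implementation measure may carry early intervention effect

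*Protocol article*

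**What the plan says.** Two sections of the protocol article give the calendar.

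- **Timing of recruitment, intervention delivery and follow-up.** On training: "Formal training of staff will begin in spring 2015". On the start of delivery: "the implementation of the new delivery system will begin in summer 2015". On full roll-out: "full project implementation will begin when schools open in September 2015 and will last for 24 months". On measurement: "Baseline assessments will be conducted during summer and fall 2015 and final assessments during summer and fall 2017". For the payment change, this section reports only early IT development and other preparation.
- **Trial status.** On deployment: "Delivery system and payment system changes will be deployed in August 2015 and January 2015, respectively". On surveys: "Data collection for the parent/caregiver/child and staff surveys will be conducted in July and August 2015 and in September and October 2017".

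Three other sections fix what these dates mean for the analysis. The program description makes payment part of the test intervention: "This new delivery system is supported by a financial incentive system for high performance". Data collection obtains the impact outcomes from "a clinical examination of children and a telephone survey of parents/caregivers and children at baseline and after 24 months", and takes process and cost outcomes from enrollment, dental-record and claims systems covering the whole enrolled population. The statistical analysis plan section models change from before to after implementation in test and control counties, and the sample size section counts 80 children per county at each of those two times.

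**The concern.** A change analysis needs a baseline taken before the intervention can act. Here the baseline window opens at about the time the delivery change starts and continues after full implementation. The stated payment date falls before the whole window, and also before the training of the staff whom the incentives are meant to motivate.

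The overlap falls mainly on the primary outcome. The surveys are dated July and August 2015, so of the two impact sources it is by elimination the clinical examination that extends into fall. Those examinations take place in community settings, the kind of place where PREDICT teams deliver preventive and caries-stabilizing services from the opening of schools.

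If test-county caries has already fallen when the baseline is taken, that fall is removed from the estimated change. Control counties have no matching loss.

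**Working it through.** **1. Dates side by side**

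| Event | Timing section | Trial status |
|---|---|---|
| Payment change | no start date; preparation only | January 2015 |
| Staff training | spring 2015 | – |
| Delivery change starts | summer 2015 | August 2015 |
| Full implementation | September 2015, for 24 months | – |
| Baseline surveys | within summer and fall 2015 | July–August 2015 |
| Baseline examinations | within summer and fall 2015 | not dated separately |
| Final surveys | within summer and fall 2017 | September–October 2017 |

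Read by measure:
- Fall examinations follow the delivery change, and the payment change if January 2015 stands.
- Surveys precede full implementation and overlap the delivery change only in August. Their clear exposure is to the payment change, if January 2015 stands.
- Records-based process and cost outcomes have no baseline visit. Their pre-period depends on which date (January, August or September 2015) counts as the start.

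**2. The plan's own power figure**

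Inputs (Sample size section): 7 versus 7 counties, 80 children per county, ICC 0.05, 25% versus 10%. A two-sided 0.05 level is stated for the satisfaction calculation and assumed here.

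- Design effect: 1 + 79 × 0.05 = 4.95. Effective n per arm: 560 / 4.95 = 113.1.
- Standard error: √[(0.25 × 0.75 + 0.10 × 0.90) / 113.1] = √(0.2775 / 113.1) = 0.0495.
- 0.15 / 0.0495 = 3.03. Noncentral t on 12 df gives 79.4%; the normal approximation gives 85.7%.

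The stated 80% is reproduced by a test-versus-control comparison at one time point. That formula contains no baseline, so a contaminated baseline does not change it.

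**3. Effect on the change contrast (illustrative)**

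Let f = (share of test-county baseline examinations made after launch) × (average share of the final effect already present at those examinations). The expected difference in differences is 15 × (1 − f) points.

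For power, the variance of the change in one arm is [(v₀ + v₁)(1 − ICC)/80 + ICC(v₀ + v₁ − 2r√(v₀v₁))]/7, where v = p(1 − p) and r is the county-level pre-post correlation. The control arm stays at 25% and the test arm goes from 25% to 10%. The documents do not give r. At r = 0.5 the standard error of the difference in differences is 0.0592; at r = 0.8 it is 0.0463. Normal approximation:

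| Assumed f | Effect (points) | Power, r = 0.5 | Power, r = 0.8 |
|---|---|---|---|
| 0 | 15.0 | 72% | 90% |
| 0.05 | 14.25 | 67% | 87% |
| 0.10 | 13.5 | 63% | 83% |
| 0.20 | 12.0 | 53% | 74% |
| 0.50 | 7.5 | 24% | 37% |

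On 12 df the first row would be 64% and 84%. No value of f can be read from the documents.

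**4. Does a late baseline always cost something?**

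Suppose the effect builds linearly, reaching 15 points at 24 months, and the baseline is k months late.
- If the final examination is equally late and the effect keeps building: 15(24 + k)/24 − 15k/24 = 15. Nothing is lost.
- If the final effect stays at 15 points: 15(1 − k/24), which is 14.4, 13.8 and 13.1 points for k = 1, 2 and 3.

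The final window is the same two seasons in 2017, but 24 months from September 2015 ends at about the start of fall 2017. Which case applies is not settled. If the effect appears quickly and then levels off, the loss is larger than under linear build-up.

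**The case against.** The strongest reply is that the overlap may matter little. The surveys largely precede full implementation. Overlap on the calendar does not show that any sampled child was treated before being examined, and prevalence may move little within weeks. The final window mirrors the baseline window, so under steady build-up the change is preserved. Process and cost outcomes come from continuous records. The primary hypothesis is worded as test versus control, and a randomised comparison at 24 months needs no baseline. All of this stands, and it limits the point. It does not remove it: the planned model is of change, and examinations made after launch are counted as pre-implementation.

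A reader might infer more than the documents support:
- **That every pre-post contrast is biased toward no effect.** Records-based outcomes are not tied to the baseline window. For satisfaction and staff scores the direction is open, since early disruption could lower the baseline and exaggerate later change.
- **That the stated 80% power falls.** It belongs to a calculation without a baseline. Loss of power applies to the change contrast and needs an assumed r and f.
- **That a late baseline costs a known number of points.** Step 4 shows the loss can be zero under the same linear assumption.
- **That January 2015 is certainly an error, or certainly right.** It fits poorly with spring training and with the preparatory stage described, but the article does not settle it.

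**Conclusion.** The point holds for the examined outcome and, if January 2015 stands, for the surveys as well. The schedule as written allows primary-outcome baseline data to be collected after the intervention has begun in the test arm only. For untreated caries the likely direction is toward no effect, on the assumption that early services already lower prevalence. The size is 15f points on a 15-point effect, with f unknown: 1.5 points at f = 0.10 and 3 points at f = 0.20, as illustrations only. Records-based process and cost outcomes are affected only through the ambiguous start date. It deserves correction because baseline data cannot be collected again later, and the Trial status section says recruitment has not begun.

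**What to change.** 1. Reconcile the Timing and Trial status sections, and state one start date for the delivery change and one for the payment change.
2. Complete baseline examinations and surveys in each test county before the first PREDICT component starts there, and measure control counties in the same weeks.
3. For records-based outcomes, end the pre-period before the earliest start date of any component, with the same calendar window in both arms.
4. If baseline examinations cannot be finished before launch (which includes the case where January 2015 is correct and the examinations stay in summer and fall 2015), pre-specify for all 14 counties that the primary caries analysis is the randomised test-versus-control comparison at 24 months. Do not switch method county by county: that would mix a change estimate with a post-only estimate according to arm and speed of roll-out.

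The cost is tighter scheduling of baseline field work and a paragraph of text. The fallback in item 4 gives up baseline adjustment for the primary outcome, but it is the comparison for which the stated 80% power was reproduced.

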## Abbreviations

ADS: Advantage dental services
CDT: Code on dental procedures and nomenclature
HIT: Health information technology
